#### Health economic analysis

For the economic evaluation, a cost-utility analysis will be conducted from both the healthcare sector and broader societal perspective. The primary outcome will be the incremental cost per quality adjusted life year gain. From the healthcare sector perspective, only direct health care costs will be included. For the broader societal perspective costs will also include indirect costs associated with work absenteeism and travel. Analyses from both perspectives will use quality-adjusted life years as the primary measure of benefit. Supplementary analyses will also provide the cost per PROMIS unit improvement and cost per x-ray avoided. Primary calculation of quality-adjusted life years will be estimated using an area under the curve approach [28]. Secondary analysis of quality-adjusted life years will estimate change in health-related quality of life over time using multi-level regression modelling with a random intercept, including time as a repeated categorical variable and adjusting for baseline scores [29]. As costs and QALYs are usually non-normally distributed [30], we will use generalised linear regression models (a priori assuming log link and gamma error which will be tested during analysis using the Pregibon link test and modified Park’s test). The 95% confidence interval estimated using the multi-level regression approach for quality adjusted life years will be presented. Uncertainty in the incremental cost per quality-adjusted life year estimate will be assessed using bootstrapping (minimum 1000 iterations) for probabilistic sensitivity analysis with 95% credible interval being reported. The incremental cost per quality-adjusted life year will be compared against a threshold willingness to pay value of $50,000 (a commonly used threshold in Australian cost–utility studies) with the sensitivity to decision making of this threshold value assessed using a cost-effectiveness acceptability analysis [31].

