#### Sample size

Sample size calculations were based on a non-inferiority hypothesis comparing POCUS with x-ray (routine care) for the primary outcome of upper limb function assessed using the PROMIS score at 4 weeks. Previous studies suggest the true between-group difference was assumed to be zero with the non-inferiority margin defined as an absolute difference of 5 points and the standard deviation of PROMIS assumed to be 11.5 points [21–23]. To achieve 90% power with a one-sided α of 0.025, we require primary outcome data for 224 children (112 per arm).

A key secondary endpoint is to assess the non-inferiority of POCUS compared with x-ray as the initial imaging strategy for children who are later confirmed by the expert panel to have buckle fractures. Previous studies suggest that the standard deviation of PROMIS for children with buckle fractures is approximately 7.5 points [21–23]. Assuming the true between-group difference is 0 and defining the non-inferiority margin as 5 points, then with 90% power and one-sided *α* = 0.025, we require primary outcome data on 96 children with buckle fractures (48 per arm). We assume 35–45% of participants will be diagnosed with buckle fractures by the expert panel.

Recruitment will continue until primary outcome data has been collected on both at least 112 children per arm and at least 48 buckle fractures per arm. Allowing for approximately 25% attrition and variation in buckle fracture prevalence, we expect to recruit up to 300 patients to achieve the required sample size.

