## Data collection and management

Data will be manually collected at the initial hospital visit, later manually entered into the secure, purpose-built web-based database, REDCap® (Research Electronic Data Capture, Vanderbilt University, Nashville, TN, USA), and then via automated electronic surveys directly linked to the database, emailed to participants after discharge at the designated timepoints, generally a combination of 1, 4 and 8 weeks (Figs. 1 and 2). If the electronic surveys have not been returned, parents will receive a phone call within 48 h to remind them to complete and submit them. A maximum of 5 attempts to contact parents or secondary contacts by either telephone, text message or email will be made by the research team. If there is no response after the 5th attempt, the participant will be considered lost to follow-up for that time point but will still be contacted at subsequent time points, unless the patient withdraws from the trial.

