### Statistical methods

Summary statistics will be presented as either mean (SD) or median (25th–75th percentile) for continuous data, depending on their distribution, and as frequency (percentage) for categorical data. For the primary outcome, physical function assessed by the PROMIS tool at 4 weeks, we assess non-inferiority of POCUS within a 5-point margin. The between-group difference at 28 days will be assessed using linear regression modelling with treatment group (POCUS/x-ray) included as a main effect. Non-inferiority will be established if the 95% confidence interval for the difference between-groups is completely above the non-inferiority margin. Primary analyses will include all randomised patients. A secondary analysis of the subgroup of patients confirmed to have buckle fractures by the expert panel will be undertaken. Analysis will be on an intention-to-treat basis, with a secondary per-protocol analysis undertaken.

Secondary outcomes such as costs, satisfaction, pain, complications, rates of imaging, length of stay and diagnostic accuracy for the two study groups will be compared. Linear regression models will be used to compare continuous outcomes, logistic regression models will be used to compare dichotomous outcomes, and Poisson regression models will be used to compare count outcomes. Subgroup analyses will be performed for each category of ‘no’ fracture, ‘buckle’ fracture and ‘other’ fracture, and also for age category (5–9 and 10–15 years), given that healing rates may differ in these age groups. Missing data will not be imputed.

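### As written, a child who misses one needed CHU9D survey has no complete area-under-the-curve QALY and leaves the cost-per-QALY estimate, because the no-imputation rule is not limited to exclude the economic analysis

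*Protocol article*

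**What the plan says.** All of the following is in the protocol article.

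- **Health economic analysis.** The main result is defined as follows: "The primary outcome will be the incremental cost per quality adjusted life year gain". For the QALY itself, "Primary calculation of quality-adjusted life years will be estimated using an area under the curve approach". QALYs are the main measure of benefit in both the healthcare-sector and the societal perspective, and uncertainty in the ratio comes from a bootstrap. A secondary QALY analysis uses a multi-level model with time as a repeated factor and baseline adjustment, and its 95% confidence interval is to be presented.
- **Data collection and management.** Surveys go out after discharge at "generally a combination of 1, 4 and 8 weeks". If contact attempts fail, "the participant will be considered lost to follow-up for that time point but will still be contacted at subsequent time points", unless the child withdraws.
- **Statistical methods.** "Missing data will not be imputed". No outcome or analysis is exempted. Health economic analysis is a subsection of this section and gives no missing-data rule of its own. The same section says "Primary analyses will include all randomised patients".
- **Health care costs.** Resource use at the initial visit is taken from electronic medical records. Later healthcare use, parent and patient time, travel and other indirect costs come from a questionnaire and are assigned to the societal perspective.
- **Sample size.** "Allowing for approximately 25% attrition and variation in buckle fracture prevalence, we expect to recruit up to 300 patients".

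**The concern.** An area under the curve is built from several utility measurements on the same child. The follow-up procedure expects some children to miss one survey and answer others. Without imputation, and with no other provision in the text, such a child has no complete area under the curve and so no QALY to pair with a cost in the bootstrap, even when most of the child's data were collected.

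The main economic estimate would then rest on children who answered every needed survey, while the 4-week PROMIS analysis needs only one. The two results could describe different groups of children, and the economic one would fall short of the all-randomised principle stated in the same section. In an open-label trial, whether a family answers may depend on recovery or on the arm, and a complete-case analysis does nothing about that. The article also ranks the method that can use partly observed children below the one that cannot.

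**Working it through.** **Step 1. The plan's own figures.** With margin 5, SD 11.5, a true difference of 0, one-sided alpha 0.025 and 90% power, the sample size is 112 per arm, as stated. With SD 7.5 it is 48 per arm, as stated. Allowing for 25% attrition, 224 / 0.75 = 298.7, or 299, against the stated 300. The 25% is therefore an allowance for having the 4-week PROMIS score, a single time point: 300 × 0.75 = 225 children.

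**Step 2. What a missed survey does under the text as written.**

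| Quantity | Source | After one missed survey |
|---|---|---|
| Area-under-the-curve QALY | CHU9D at each needed survey | incomplete |
| Initial-visit cost | medical record | kept |
| Later and indirect cost (societal) | questionnaire | incomplete |
| Cost-per-QALY pair, healthcare sector | cost and QALY | lost, for want of a QALY |
| Cost-per-QALY pair, societal | cost and QALY | lost, for want of both |
| Secondary multi-level QALY model | observed utilities | kept |

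**Step 3. How many children might be affected.** The article gives no miss rate per survey, and the CHU9D schedule is in a figure that is not shown. Assumptions: baseline is complete, k follow-up surveys are needed, and a fraction d misses each one.

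- Same children always miss: complete fraction = 1 − d.
- Independent misses: complete fraction = (1 − d)^k.
- In between: each child has a normal latent tendency to miss, correlated rho between surveys.

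| d | k | Same children | rho 0.8 | rho 0.5 | Independent |
|---|---|---|---|---|---|
| 25% | 3 | 75% (225 of 300) | 62% | 54% | 0.75³ = 42% (127) |
| 25% | 2 | 75% (225) | 67% | 62% | 0.75² = 56% (169) |
| 10% | 3 | 90% (270) | 83% | 78% | 0.90³ = 73% (219) |
| 5% | 3 | 95% (285) | – | – | 0.95³ = 86% (257) |

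At d = 25% and k = 3, the children who answer some but not all surveys are 24% of the total at rho 0.8 and 39% at rho 0.5. These are the children whose collected utilities the primary QALY would not use. If the same children always miss, this group is empty and the economic analysis loses no more than PROMIS does.

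**The case against.** **The area under the curve need not use every survey.** A trapezoid can be drawn across a missed middle survey. That is possible, but the article does not provide for it. It amounts to assigning a value on the line between the neighbours, and it cannot recover a missing last survey.

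**The analysis plan may settle this.** Detail on missing data is commonly left there, and the analysis plan is not shown. But the article does not leave the matter open: it states a rule, and an analysis plan that imputed utilities would contradict it. One can argue that the sentence, which closes the paragraph on secondary outcomes and subgroups, was never meant for the economic subsection. If so, saying so is part of the remedy.

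**The multi-level model already keeps these children.** It does, and its interval will be presented. It is nevertheless secondary and is not stated to feed the cost-per-QALY estimate, the bootstrap or the acceptability analysis.

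**The loss may be small.** This stands. The 25% is a recruitment allowance for one endpoint, not a rate per survey. Reminders, questionnaires completed by phone and up to five contact attempts may keep misses low. A reader might infer that a large share of children will drop out of the economic results, but no figure in the documents supports that.

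**Costs are not all lost.** This also stands. A reader might infer that a missed survey removes a child's total cost. On the article's wording that applies to the societal perspective only. The supplementary cost per x-ray avoided and cost per PROMIS unit do not need the CHU9D at all.

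**Conclusion.** The point holds in a limited form. Three statements in the article (an area-under-the-curve QALY as the primary calculation, continued follow-up after a missed survey, and an unqualified rule against imputation) together remove partly observed children from the cost-per-QALY estimate in both perspectives.

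The size is unknown. If 25% missed each of three surveys, 42% to 75% of children would be complete, with 54% and 62% at latent correlations of 0.5 and 0.8. At 10% per survey the range is 73% to 90%. These figures rest on an assumed miss rate, an assumed number of CHU9D surveys and a complete baseline. At the upper end of each range there is no loss beyond that for PROMIS at the same miss rate. No bias has been demonstrated; the exposure is to lost precision and to possible selection.

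The economic evaluation is a secondary objective and the non-inferiority conclusion on PROMIS is untouched. The change is still worth making before the data are analysed, because the remedy is cheap and uses data already to be collected.

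**What to change.** 1. Limit the no-imputation sentence so that it does not cover the health economic analysis.
2. Choose one primary approach for the cost-per-QALY estimate. Either multiply impute missing utilities at each survey and missing survey cost items, separately by arm, and combine this with the bootstrap of cost and QALY pairs; or take the QALY difference from the planned baseline-adjusted repeated-measures model, turning its arm-by-time means into QALYs with area-under-the-curve weights and refitting it in each bootstrap sample. The second option deals with utilities only, so survey costs in the societal perspective would still need imputation.
3. Keep the complete-case area under the curve as a sensitivity analysis, and report how many children per arm contribute to it.

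The cost is a few sentences and some programming; no new data are needed. Both options rely on data being missing at random given what is observed, and the plan should state that assumption.

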### Objectives

The primary objective of this trial is to assess whether, in children presenting to ED with distal forearm fractures, initial diagnostic imaging modality (POCUS compared to x-ray) affects functional upper limb outcomes. A secondary objective includes a health economic analysis to determine the cost-effectiveness of POCUS compared to x-ray as the initial imaging. We hypothesise that when POCUS, instead of x-ray, is used as the initial diagnostic tool for paediatric distal forearm fractures, upper limb physical function is non-inferior at 28 days post injury, with an overall reduction in x-rays and costs, without missing any clinically significant fractures.

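### The primary economic result is an ICER with an interval, read against $50,000; if QALY differences straddle zero the interval cannot be interpreted, and net monetary benefit would be the safer decision statistic

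*Protocol article*

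**What the plan says.** The Health economic analysis section of the protocol article plans a cost-utility analysis from a healthcare-sector and a societal perspective. "The primary outcome will be the incremental cost per quality adjusted life year gain." The precision of that ratio is to be described by resampling: "Uncertainty in the incremental cost per quality-adjusted life year estimate will be assessed using bootstrapping (minimum 1000 iterations"), with a 95% credible interval reported. The decision step is "The incremental cost per quality-adjusted life year will be compared against a threshold willingness to pay value of $50,000", and the sentence goes on "with the sensitivity to decision making of this threshold value assessed using a cost-effectiveness acceptability analysis". Net monetary benefit is not mentioned, and nothing is said about a QALY difference at or below zero. Supplementary ratios are cost per PROMIS unit and cost per x-ray avoided.

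On QALYs: "Primary calculation of quality-adjusted life years will be estimated using an area under the curve approach". A multi-level model is secondary, "including time as a repeated categorical variable and adjusting for baseline scores". The section then says that the QALY confidence interval to be presented is the one from the multi-level model. Generalised linear models are named for costs and QALYs, without a list of covariates.

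Two other sections show the result the trial expects. Objectives hypothesises that "upper limb physical function is non-inferior at 28 days post injury, with an overall reduction in x-rays and costs". Sample size says of PROMIS that "the true between-group difference was assumed to be zero with the non-inferiority margin defined as an absolute difference of 5 points".

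**The concern.** An ICER compared with a single threshold presupposes a QALY gain. This trial is built around the expectation that POCUS does about as well and costs less. If the QALY difference is also close to zero, the denominator of the primary economic statistic can take either sign. Three things then go wrong. The same ratio can describe opposite situations. The meaning of being below the threshold reverses when QALYs are lower. A percentile interval for the ratio mixes values that cannot be ordered from good to bad.

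Cost-effectiveness is a named secondary objective, so a reader will look for a clear answer here. A lesser issue is that the QALY estimate called primary and the QALY interval promised belong to different analyses.

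**Working it through.** **Inputs from the protocol.** Threshold W = $50,000 per QALY; follow-up 8 weeks; 112 per arm with primary outcome data; PROMIS SD 11.5, margin 5, true difference 0. The economic section has no figure to reproduce. The sample size does reproduce: 2 × 11.5² × (1.960 + 1.282)² / 5² = 111.2, rounded up to 112.

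**Assumptions, not in the protocol.** SD of 8-week QALYs 0.005 to 0.02; mean saving with POCUS $50 to $100; SD of cost $100 to $300; true QALY difference 0.

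**Step 1: where the threshold comparison reverses.** Let dC and dQ be the cost and QALY differences (POCUS minus x-ray), and NMB = W × dQ − dC. If dQ > 0, dC/dQ < W is the same statement as NMB > 0. If dQ < 0, multiplying through by dQ turns the inequality round, so dC/dQ < W means NMB < 0. The two rules disagree exactly when dQ is negative.

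| dC | dQ | ICER | NMB at $50,000 |
|---|---|---|---|
| −$100 | −0.001 | $100,000 | +$50 |
| −$100 | −0.004 | $25,000 | −$100 |
| −$100 | +0.001 | −$100,000 | +$150 |
| +$100 | −0.001 | −$100,000 | −$150 |

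In row 1 POCUS is preferred although its ICER is above the threshold; in row 2 it is not preferred although its ICER is below. Rows 3 and 4 share one ICER, but POCUS dominates in one and is dominated in the other.

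**Step 2: scale of the QALY difference.** The maximum over 8 weeks is 56/365.25 = 0.153 QALY. A utility difference of 0.05 lasting all 8 weeks is worth only 0.05 × 0.153 = 0.0077. The standard error of dQ is SD × √(2/112), which is 0.0007 to 0.0027 over the assumed SDs.

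**Step 3: the two intervals.** One million simulated pairs (dQ, dC) per scenario gave these 2.5th and 97.5th percentiles of the ICER:
- QALY SD 0.005, saving $100, cost SD $300: −$2.40 million to +$2.41 million.
- QALY SD 0.02, saving $100, cost SD $300: −$0.60 million to +$0.60 million.
- QALY SD 0.02, saving $50, cost SD $100 (the narrowest): −$0.30 million to +$0.30 million.

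For NMB the standard error is √[(50,000 × SE of dQ)² + (SE of dC)²]. In the first scenario it is √(33.4² + 40.1²) = 52.2, giving $100 ± 1.96 × 52.2 = −$2 to $202. In the second it is √(133.6² + 40.1²) = 139.5, giving −$173 to $373. Both can be read directly against zero.

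**Step 4: cost per PROMIS unit.** This needs only the protocol's figures. The standard error of the PROMIS difference is 11.5 × √(2/112) = 1.54, so with the assumed true difference of 0 the estimate lies within ±1.96 × 1.54 = ±3.0 points in 95% of trials. Its 95% interval would then exclude zero in only 5% of trials. Cost per x-ray avoided is different, because the trial expects fewer x-rays and so a denominator away from zero.

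**Step 5: baseline utility.** With an assumed utility SD of 0.10 to 0.20, a chance baseline imbalance has standard error 0.013 to 0.027. Take an imbalance of 0.03. Through the baseline point alone it adds 0.03 × 0.5/52 = 0.0003 QALY ($14 at the threshold) if the first follow-up utility is at 1 week, or 0.03 × 2/52 = 0.0012 QALY ($58) if it is at 4 weeks. If it persisted for all 8 weeks it would add 0.03 × 0.153 = 0.0046 QALY ($230).

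**The case against.** The strongest reply is that the protocol only says the ICER will be compared with $50,000. It does not say that any value below it favours POCUS, and a health economist would read the ratio by quadrant. The same sentence plans an acceptability analysis. Built in the usual way, that analysis gives the probability of positive net benefit at each threshold, $50,000 included, and handles all four quadrants. This stands as mitigation. However, the text gives that analysis the job of testing sensitivity to the threshold, while the primary outcome and the reported interval remain those of the ratio.

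The document supports none of these stronger readings:
- *That half the bootstrap replicates will mislead.* In the simulation the two rules disagree in about 50% of draws, but this only restates the assumed zero true QALY difference. Replicates in the real trial will centre on the observed difference, and the share below zero could be anywhere from near none to near all.
- *That the QALY difference is expected to be zero.* The zero in Sample size is for PROMIS at 4 weeks. If POCUS is cheaper and QALYs are higher, it dominates and nothing reverses.
- *That the primary QALY comparison is unadjusted.* Area under the curve is how each child's QALYs are calculated. The covariates of the generalised linear models are not listed, and a condensed article may leave them to the full plan.
- *That the Discussion lets the ICER decide the choice of imaging.* It names cost, patient preference and pain. Cost is compared directly under Statistical methods.

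**Conclusion.** The point holds in a limited form. The protocol commits to a ratio, an interval for it and a threshold comparison as the main economic result, in a trial that hypothesises non-inferior function at lower cost. If the QALY replicates straddle zero, that interval cannot be interpreted; where POCUS is cheaper with fewer QALYs, an ICER below $50,000 counts against it. The algebra needs no assumptions. The widths (ICER limits of about ±$0.3 million to ±$2.4 million) rest on the assumed costs, SDs and zero QALY difference. Whether the problem arises depends on an observed QALY difference that the document does not predict.

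Two smaller points stand on the text alone. Cost per PROMIS unit divides by a quantity whose true value the sample size calculation sets to zero, though it is only supplementary. The QALY confidence interval to be presented comes from the secondary model, not from the area-under-the-curve estimate called primary. Baseline adjustment is a recommended improvement, not a proven omission, and its direct effect is modest.

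The sample size and the non-inferiority conclusion on function are untouched.

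**What to change.** - Make incremental net monetary benefit at $50,000, with its bootstrap 95% interval, the decision statistic from each perspective.
- Keep the acceptability curve and show the cost-effectiveness plane. Report the ICER only with its quadrant, and without an interval if the replicates span quadrants.
- Omit cost per PROMIS unit if the PROMIS difference is not distinguishable from zero.
- Adjust the primary area-under-the-curve QALY comparison for baseline CHU9D, as the secondary model already adjusts for baseline scores, and report the confidence interval from that same model.

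The cost is a few sentences in the analysis plan. The bootstrap output already planned is enough, and no new data are needed. The price is a less prominent ICER, which some readers will look for first.
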